### Assessment and follow-up

#### Study procedures

The study procedures are listed in Table 3. The preoperative study procedures will take place during visits to the outpatient clinic. These visits will be routinely scheduled and will not be planned as study-specific procedures. During the first visit, the trial will be explained and patients will receive an information letter. Informed consent will be signed during a second preoperative visit. During this visit, the study medication will be provided along with instructions for use and a study diary. Furthermore, the first rectal swab will be taken and patients will receive the first quality-of-life questionnaire. The study diary will be used to document the intake of study medication and to report potential side effects due to the study medication. Patients will take the study medication according to the instructions during the 3 days prior to surgery. The bottles with remainders of study medication will be collected at hospital admission and will be weighted to estimate treatment adherence. The study diaries will also be collected at admission.

**Table 3 Tab3:** Study flow

	Study period							
	Screening^b^	Enrollment^b^	Intervention			Follow-up and postoperative procedures^c^		
			day					
Time point^a^	~ − 2 weeks	~ − 2 weeks to day − 4	−3	−2	−1	Day 0	Day 30	Month 6
Patient recruitment	X							
Eligibility screening		X						
Informed consent		X						
Allocation		X						
Rectal swab		X					X	
Intake study medication			X	X	X			
Surgery						X		
Estimation of compliance			X	X	X			
Patient characteristics	X	X						
Surgical characteristics						X		
Primary endpoint Deep SSI and/or mortality							X	
Secondary endpoints								
Superficial SSI							X	
Anastomotic leakage							X	
Re-laparotomy							X	
Bacteremia							X	
Rectal colonization with HRE or colistin resistant species							X	
Infection with HRE							X	
Infection with *Clostridium difficile*							X	
In-hospital antibiotic use							X	
Length of hospital stay								X
Length of ICU stay								X
All-cause mortality							X	X
In-hospital costs								X
Quality of life		X						X
Adverse events		X	X	X	X	X	X	X
Serious adverse events		X	X	X	X	X	X	X
SUSARs/SARs			X	X	X	X		

*HRE* highly resistant *Enterobacteriaceae*, *ICU* intensive care unit, *SAR* serious adverse reaction*, SSI* surgical site infection, *SUSAR* serious unexpected adverse reaction

^a^The day of surgery is referred to as day 0. The exact time points of the first and second preoperative visits to the outpatient clinic will depend on the local schedules and procedures

^b^Screening and enrollment are performed during visits to the outpatient clinic. These visits are not study-specific and are planned according to the local logistics

^c^The postoperative data collection is performed by assessment of the patient registers. A phone call will be made at around day 30 and month 6 to assess the status of the patient and to remind the patient to perform the rectal swab (day 30) and fill in the questionnaire (month 6)

Patients will be followed until 6 months after surgery to evaluate the development of primary and secondary outcomes. The data on almost all of these outcomes, including infectious complications will be documented as part of daily practice. Thirty days after surgery, the medical records will be assessed to collect data on primary and secondary outcomes and a second rectal swab will be taken by either the patient or by a member of the local study team. Six months after surgery, the medical records will be assessed again to collect additional data on readmissions and length of hospital stay, including admissions to the ICU. Furthermore, patients will receive the second quality-of-life questionnaire. After the questionnaire has been completed and sent back to the study team, the follow-up is completed.

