#### Adverse events

Pre-OP consists of non-absorbable antibiotics. When taken orally, there is virtually no uptake of antibiotic components in the bloodstream. It is, therefore, expected that the occurrence of systemic side effects is negligible. More importantly, there is extensive experience with non-absorbable antibiotics applied as SDD on ICUs and severe and acute side effects that could apply to the current study have not been reported [27–30]. For this reason, we decided to refrain from an obligatory observation period after intake of the first dose of the study medication and patients can, therefore, take the medication at home. Nevertheless, patients will receive information about severe side effects of this study medication and are instructed to seek medical advice when they might suffer from severe acute side effects. The unblinding protocol can be freely assessed via our website, when deemed necessary. Late side effects, such as the development of antibiotic resistance, have not been described either [31–35]. Nevertheless, the occurrence of side effects and the development of antibiotic resistance will be monitored as secondary endpoints of this study.

All adverse events will be reported to the principle investigator. Serious adverse events (SAEs), serious adverse reactions (SARs) and suspected unexpected serious adverse reactions (SUSARs) will be reported to the sponsor within 24 h after notification of the event. For the SAEs, we decided to only report life-threatening infections with colistin- or tobramycin-resistant bacteria or *C. difficile* colitis within 24 h. Postoperative complications that are known to occur after colorectal surgery and are not directly related to the study medication will be reported to the ethical board in periodic line-listings and not within the 24-h time window.

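### The home diary is described as recording side effects of the study medication, which is narrower than the all-adverse-events scope the protocol sets for the three dosing days

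*Protocol article*

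**What the plan says.** Under Study procedures the article states the purpose of the diary: "The study diary will be used to document the intake of study medication and to report potential side effects due to the study medication". It adds: "The study diaries will also be collected at admission". Returned bottles are handled at the same contact: "The bottles with remainders of study medication will be collected at hospital admission and will be weighted to estimate treatment adherence".

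Table 3, in the same section, has a row for adverse events and a row labelled "Serious adverse events". Both are marked at enrollment, on days -3, -2 and -1, and at day 0, day 30 and month 6. Neither is limited by presumed cause. Reactions (SUSARs/SARs) have a separate row.

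Under Adverse events, the reporting scope is unrestricted: "All adverse events will be reported to the principle investigator". The same section says that the occurrence of side effects is monitored among the secondary endpoints. It also describes the setting. The investigators write that "we decided to refrain from an obligatory observation period after intake of the first dose of the study medication", so "patients can, therefore, take the medication at home". Patients are "instructed to seek medical advice when they might suffer from severe acute side effects".

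**The concern.** An adverse event is recorded whether or not the drug caused it. A side effect is an event already attributed to the drug. A diary that asks for the second has the patient apply a causality filter before anything is written down. In a double-blind randomised trial, attribution is better drawn from comparing all events between the arms, because a patient cannot tell a drug effect from the disease, anxiety or a change of diet before surgery.

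What is at stake is the safety record for days -3 to -1, the only days on which study medication is taken. Unexpected effects are the ones that a patient is least likely to attribute to the medicine, so a filter of this kind would tend to miss them first. The prior experience that the article cites for safety comes from intensive care units. This trial gives the drug to elective patients at home, and a cause-neutral record of those days would be informative in its own right.

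**Working it through.** No arithmetic applies. The check is whether what the article says is to be collected on the dosing days matches the means it describes for collecting it.

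**Scope required on days -3 to -1**

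- Table 3: adverse events and serious adverse events, no causality limit.
- Adverse events section: all adverse events go to the principal investigator.
- Table 3 keeps reactions in a row of their own, so the plan itself distinguishes events from drug-attributed events.

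**Means described for those days**

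| Source | What it is described as giving | Elicits a mild event that the patient does not link to the drug? |
|---|---|---|
| Diary | Drug intake, and potential side effects of the medication | Not as worded |
| Weighed bottles | Adherence | No |
| Patient seeks medical advice | Severe acute side effects | No |
| Collection at admission | Diary and bottles handed in; no adverse-event question mentioned | Not stated |
| Postoperative registers; calls at about day 30 and month 6 (Table 3 footnote) | Postoperative data; patient status and reminders about swab and questionnaire | Not described as covering these days |

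**Reading the two together**

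1. The diary wording corresponds to the reaction concept, not to the unrestricted row in Table 3.
2. No other source described for the dosing days fills the difference for mild, unattributed events.
3. Table 3 and the reporting sentence set out what is to be collected. They do not say how such events at home come to anyone's notice.
4. The article does not leave the diary's purpose open. It states it, and the stated purpose is narrower than the scope stated elsewhere. If the real form is broader, the Study procedures text misdescribes it. If it is not, collection is narrower than intended. In either case the passages need reconciling.

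**The case against.** The strongest reply is that this is a condensed article. The diary form, the eCRF fields and the full protocol are not shown, and the detail of how events are elicited is commonly left to them. That stands against three stronger conclusions that a reader might draw:

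- **That the diary is the sole routine record of the dosing days.** The article never says so. The weighed bottles are also a routine record, though only of adherence.
- **That there is no study contact over this period.** The article says that patients may take the medication at home. It does not exclude contact, and admission is a staff contact directly after dosing at which events could be asked about.
- **That adverse events on these days are lost.** Table 3 schedules them on each dosing day, and the Adverse events section requires all of them to be reported. The most that follows is that no described instrument elicits the mild, unattributed ones.

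A second reply is that the diary asks for potential side effects, not established ones. A patient taking a new medicine four times a day could reasonably enter any new symptom. This softens the filter but does not remove it, since the phrase still ties the entry to the study medication.

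A third reply is that the harm cannot be sized. That also stands. It is tempting to assume event rates and a recorded fraction and to quote a loss of power. The article gives neither figure and sets no power target for tolerability. Even the direction depends on the assumption: losing background and drug-caused events in equal proportion weakens the comparison, whereas losing mainly background events could sharpen it.

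Finally, the expectation of negligible side effects concerns systemic effects only. It rests on minimal absorption and intensive care experience, not on diary data, so the diary wording does not undermine that argument.

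**Conclusion.** The point holds as a mismatch of scope. The diary is the only safety instrument that the article describes for home dosing, and its stated content is narrower than the adverse-event scope in Table 3 and in the Adverse events section. Mild events that patients do not connect with the medication may therefore go unrecorded on days -3 to -1.

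Severity is minor. Patients, treating physicians and outcome assessors are blinded, so under-recording is likely to be similar in the two arms, although equal under-recording would still lower both observed rates. The primary endpoint and the sample size are unaffected. The size of any loss cannot be derived from the document.

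The conclusion assumes that the diary form matches its description and that staff do not ask about all events at admission. If either assumption is wrong, what remains is a correction to the text.

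**What to change.** Word the diary so that, from first dose until surgery, the patient records every new or worsened symptom whatever its presumed cause. Let the blinded investigator assign causality afterwards, and compare events in this window by arm. If staff already ask about all events when they collect the diary at admission, say so in Study procedures; that sentence would bring the text into line with Table 3 and the Adverse events section without changing the form.

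The cost is a change to the diary form and one additional table by arm, or a single sentence if the practice already exists. No extra visit, patient or procedure is needed. The downside is more minor, unrelated symptoms to enter and code.

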#### Retention and withdrawal of participants

Patients are free to withdraw from the study at any time, which is in accordance with the Dutch law on medical research on humans. When patients are unwilling to have the rectal swab taken or to fill in the questionnaire, these data will considered to be missing and will be dealt with in data analysis using the appropriate methods.

The intention-to-treat principle will be applied to our primary analysis to deal with poor or non-compliance to the study medication, as this is likely to reflect daily practice. The remainders of study medication will be weighted to estimate the compliance. To enhance the compliance, patients are informed about the bitter taste of the treatment and are advised to take the study medication together with other drinks to mask the taste. Another strategy that will be applied to enhance retention of patients is to call the patients on the two postoperative follow-up moments to remind them about the rectal swab requirement and the questionnaire that will be send to their home address.

#### Microbiological methods

Clinical cultures will be performed and processed in the local microbiology laboratory of the participating centers according to the routine laboratory procedures. Date of culture, specimen type, species cultured, antimicrobial susceptibility and the production of extended-spectrum beta-lactamase or carbapenemase will be documented. Fecal samples from patients who develop nosocomial diarrhea will be tested for the presence of *Clostridium difficile* toxins, according to routine laboratory procedures and based on the indication by the attending physician.

Rectal swabs will be pre-enriched and subsequently cultured using selective media, aimed at the detection of extended-spectrum beta-lactamase (ESBL)-producing *Enterobacteriaceae* and carbapenem-, tobramycin- and colistin-resistant, Gram-negative bacterial species’ identification and antimicrobial susceptibility testing will be performed for all isolates that grow on either one of the screening agars. Phenotypic ESBL confirmation will be performed with the combination disk diffusion method according to the NVMM guideline on the laboratory detection of highly resistant microorganisms (HRMO).

### Data management

An electronic Case Report Form (eCRF) will be used for each patient to collect all data on baseline patient characteristics and outcomes (Additional file 1). The data management department of the Julius Center for Health Sciences and Primary care at the UMC Utrecht developed the eCRF which is hosted by ResearchOnline.

Patients will receive a unique identification number at inclusion. The list with the unique identification numbers linked to the patient will be securely stored at the study site where the patient is included. This list will be the only way to trace the identification numbers back to the individual patients. When the data are entered in the eCRF, patients will be identified with the unique identification number. No patient numbers, names, addresses or complete dates of birth will be recorded.

### Statistical analysis

The primary composite endpoint will be analyzed according to the intention-to-treat principle. All patients who were randomized to receive study medication and who underwent colorectal surgery will be included in this analysis. The difference in the primary outcome between Pre-OP and placebo will be estimated with a Z-test for proportions or by logistic regression, correcting for the stratification variable (study site). Multivariable logistic regression will be used and measured confounders will be fitted in the model as covariates. Secondary outcomes will be analyzed using the chi-square test, Fisher’s exact test, logistic regression, time-to-event analysis, *t* test or Mann–Whitney *U* test, when appropriate. Missing data will be analyzed and handled using.

Exploratory subgroup analyses will be performed for study center, age, sex, Body Mass Index (BMI), ASA classification, preoperative use of immunosuppressive drugs, preoperative radiation of the surgical site, indication for surgery, wound class, surgical procedure, duration of surgery and timing of perioperative intravenously administered antibiotic prophylaxis. Per-protocol analyses will be performed in addition to all the intention-to-treat analyses.

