### Outcome measures

As a primary composite endpoint, we will investigate the efficacy of Pre-OP on deep SSI and/or mortality within 30 days after surgery. The secondary endpoints including their definitions are summarized in Table 2.

**Table 2 Tab2:** Definition of endpoints

Endpoints	Definitions
Primary composite endpoint	
Cumulative incidence of deep surgical site infection and/or mortality within 30 days after surgery	Deep SSI will be diagnosed according to the CDC criteria for surgical site infections [37]. Deep SSI includes both deep incisional SSI and organ/space SSI
Secondary endpoints	
*30 days after surgery*	
Cumulative incidence of superficial SSI	Superficial and deep SSIs will diagnosed according to the CDC criteria for surgical site infections [37]
Cumulative incidence of deep SSI	
All-cause mortality	
Cumulative incidence of bacteremia	Blood cultures positive for microorganisms
Cumulative incidence of infection with *Clostridium difficile*	Stool sample positive for *C. difficile* toxins
Cumulative incidence of infection with HRE	Clinical cultures positive for ESBL or carbapenemase-producing *Enterobacteriaceae* or *Enterobacteriaceae* resistant to quinolones and/or aminoglycosides [38]
Cumulative incidence of rectal colonization with HRE and colistin resistant species	Rectal swabs positive for HRE or colistin resistant species, measured at baseline and 30 days after surgery
Cumulative incidence of anastomotic leakage	Clinical and/or radiological evidence of leakage requiring surgical or radiological reintervention
Cumulative incidence of re-laparotomy	Reoperation in the abdominal region
In-hospital use of antibiotics	Defined as “days on therapy”
*6 months after surgery*	
All-cause mortality	
Quality of life	Measured with the RAND-36 questionnaire [39]
Length of hospital stay	In days, including all readmissions
Length of ICU stay	In days, including all readmissions
In-hospital costs	

*CDC* Centers for Disease Control and Prevention, *ESBL* extended-spectrum beta-lactamase, *HRE* highly resistant *Enterobacteriaceae*, *ICU* intensive care unit, *SSI* surgical site infection

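### The methods listed for secondary outcomes include no baseline-adjusted model for RAND-36, although the questionnaire is collected at enrolment and at 6 months

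*Protocol article*

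**What the plan says.** Table 2 (Outcome measures) places quality of life among the 6-month secondary endpoints, "Measured with the RAND-36 questionnaire". The Study procedures section schedules two measurements. At the preoperative visit where consent is signed and study medication is handed out, "patients will receive the first quality-of-life questionnaire". At 6 months after surgery, "patients will receive the second quality-of-life questionnaire". Table 3 agrees, marking quality of life at enrolment and at month 6.

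The Statistical analysis section covers all secondary outcomes in one sentence, which opens "Secondary outcomes will be analyzed using the chi-square test". The list continues with logistic regression, Fisher's exact test and time-to-event analysis, and ends with the t test or Mann–Whitney U test, each where appropriate. No test is assigned to quality of life, and the section does not say whether the 6-month score or the change from baseline is compared. Covariates appear in one place, for a binary outcome model: "Multivariable logistic regression will be used and measured confounders will be fitted in the model as covariates". Correction for study site is mentioned only for the primary outcome, although randomization is stratified by center.

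Under Retention and withdrawal of participants, the article expects some questionnaires not to be completed and says "these data will considered to be missing and will be dealt with in data analysis using the appropriate methods". It gives no expected return rate.

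**The concern.** A questionnaire completed before treatment is usually informative about the same questionnaire completed later, and collecting it lets the analysis remove variation between patients that has nothing to do with treatment. The listed methods do not do this for a continuous score. Chi-square, Fisher's exact test and logistic regression are for categorical outcomes, and time-to-event analysis does not fit a scale score. That leaves two unadjusted two-sample tests.

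At stake is the width of the confidence interval for the quality-of-life difference. There is also an open choice. The two scores to which a t test could be applied differ in precision, in a direction that depends on a correlation nobody knows yet, and the article does not say which would be used.

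**Working it through.** **Figure in the plan.** The article states no power or precision target for quality of life, so there is none to reproduce. Its only sample-size figure, 966, belongs to the primary endpoint. With risks of 14% and 14% × (1 − 0.40) = 8.4%, one-sided 2.5% and 80% power, the unpooled formula gives (1.960 + 0.842)² × (0.14 × 0.86 + 0.084 × 0.916) / 0.056² = 493.9 per arm. That is 988 in total, within 3% of 966. Nothing below affects that figure.

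**Inputs for quality of life.**
- From the article: two RAND-36 measurements, 1:1 allocation, 966 patients (483 per arm).
- Assumed: correlation ρ between baseline and 6-month score of 0.3 to 0.7, equal SD at both times, SD 20 points, and 400 patients per arm with both questionnaires (400/483 = 83%).

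**Step 1: variance relative to a t test on the 6-month score.**
- Change score: 2(1 − ρ)
- ANCOVA: 1 − ρ²

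| ρ | 6-month score only | Change score | ANCOVA |
|---|---|---|---|
| 0.3 | 1.00 | 1.40 | 0.91 |
| 0.5 | 1.00 | 1.00 | 0.75 |
| 0.7 | 1.00 | 0.60 | 0.51 |

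The ratio of ANCOVA to change score is (1 − ρ²)/(2(1 − ρ)) = (1 + ρ)/2, which is below 1 for any ρ below 1. ANCOVA is therefore the most precise of the three in every row. Below ρ = 0.5 the change score is worse than leaving the baseline out. These factors describe the t test; the Mann–Whitney test was not computed separately.

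**Step 2: difference detectable with 80% power, two-sided 5%.** Formula: 2.80 × 20 × √(2 × factor / 400).
- 6-month score only: 56 × √0.005 = 3.96 points
- Change score: 4.69, 3.96 and 3.07 points at ρ = 0.3, 0.5 and 0.7
- ANCOVA: 3.78, 3.43 and 2.83 points at the same values

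**Step 3: the same without assuming an SD.** With all 966 analysed, the detectable difference under the 6-month-only t test is 2.80 × √(2/483) = 0.180 SD. Under ANCOVA it is 0.172, 0.156 or 0.129 SD. With an assumed 80% return (773 patients), it falls from 0.202 SD to 0.192, 0.175 or 0.144 SD.

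**Step 4: equivalent in patients and power.** The unadjusted 6-month test would need 966/(1 − ρ²) = 1062, 1288 or 1894 patients to match ANCOVA on 966. A true difference that the unadjusted test detects with 80% power would be detected by ANCOVA with 83.6%, 89.9% or 97.5% power.

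**The case against.** A reader might infer that the trial will compare quality of life with no use of the baseline score. The article does not support that. It ties no test to RAND-36, its list is generic and qualified, and a t test on the change from baseline would use the first questionnaire. What can be said is narrower: no listed method adjusts a continuous outcome for its baseline value.

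A reader might also infer bias, or exposure to chance baseline imbalance as a flaw. Neither follows. Under 1:1 randomization a two-sample comparison of 6-month scores or of changes is valid, and chance imbalance is already reflected in its standard error and type I error.

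The strongest objection is that the model for one of many secondary endpoints is detail that a journal article leaves to the statistical analysis plan, which is not at hand and may already specify ANCOVA. That limits the weight of the point. It does not remove it, because the article does more than stay silent: it names the methods, and the two that fit a continuous score are poorly matched to the data it collects.

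The size is also open to challenge. The correlation is not in the documents, and with surgery between the two measurements a low value is plausible. At 0.3 the variance falls by only 9%. That objection stands as to size. It does not change the ranking of the methods.

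**Conclusion.** The point holds as a free improvement. Both RAND-36 measurements are planned, and the methods listed for a continuous score include no model that conditions on the baseline. Relative to a t test on the 6-month score, adjustment would reduce the variance by 9%, 25% or 49% at assumed correlations of 0.3, 0.5 or 0.7. With an assumed SD of 20 and 400 per arm, the detectable difference falls from 4.0 to about 3.8, 3.4 or 2.8 points. Relative to change scores, the variance falls by 35%, 25% or 15% (1 − (1 + ρ)/2).

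The loss is of precision on one secondary endpoint. The primary analysis, the sample size of 966 and the interim decision are not affected. The existence of the gap rests on the article's text; its size rests on the assumed correlation, the equal SDs and the questionnaire return.

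**What to change.** State that each RAND-36 scale at 6 months will be analysed by linear regression (ANCOVA) with treatment, baseline score and study site (the randomization stratum) as terms, reporting the adjusted mean difference with its 95% confidence interval. Keep the Mann–Whitney U test as a sensitivity analysis only. This also settles, before unblinding, which score is compared.

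The cost is one sentence in the analysis plan, or a check that the plan already contains it. No new data, visits or patients are needed. The change does not by itself deal with deaths before 6 months, unreturned questionnaires or multiplicity across scales; those need their own statements.

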#### Sample size

The sample size is calculated to be 966 patients, based on a one-sided type I error of 2.5%, a type II error of 20% and an assumed 40% reduction on the absolute risk for the primary outcome in the intervention group. The absolute risk of the primary outcome is assumed to be 14%. Furthermore, one interim analysis will be conducted halfway using O’Brien-Fleming type of boundaries, with the possibility of stopping the trial for efficacy in case of overwhelming treatment effect. The absolute risk and the 40% relative risk reduction based on unpublished data from a 4-year survey of a Dutch teaching hospital, where identical preoperative orally administered antibiotic prophylaxis was introduced as standard of care.

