### Assignment of interventions

#### Randomization

After enrollment, patients will be randomly assigned to one of two treatment arms in a 1:1 ratio.

The randomization will be performed using a permuted block design with varying block sizes and stratification per study center. An independent pharmacist form Stichting Apotheek Haarlemse Ziekenhuizen, who will also be in charge of the production of the study medication, will perform the randomization. The pharmacy will provide the study medication in identical containers that will be sequentially numbered with unique medication numbers. These numbers will correspond to the treatment allocation, and will be documented on the allocation list. This list will be guarded by the hospital pharmacist of the Amphia Hospital (Breda, The Netherlands) who will coordinate the distribution of the study medication to the study centers. Members of the local study teams will be instructed to distribute the study medication according to the allocation sequence. The unique study medication identification numbers will be linked to the subjects at enrollment on a subject identification log.

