#### Interim analysis

One interim analysis will be performed when 50% of the participants completed the 30-day follow-up. The Z-statistic for the standardized treatment effect will be computed and compared with the O’Brien-Fleming type of boundaries for both efficacy and futility. Recruitment will stop if the Z statistic is larger than the efficacy boundary. The futility boundaries are non-binding and thus suggestive. The unblinded results of the interim analysis will be presented to an independent Data Safety and Monitoring Board (DSMB).

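### Centre-stratified randomisation is carried into the primary analysis but not required for the secondary ones: a minor loss of efficiency if centres differ

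*Protocol article*

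**What the plan says.** The Randomization section of the protocol article states: "The randomization will be performed using a permuted block design with varying block sizes and stratification per study center". Allocation is 1:1.

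The Statistical analysis section takes this up for the primary endpoint. The comparison is a Z-test for proportions or a logistic regression, with correction for study site as the stratification variable.

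For the other endpoints the same section reads "Secondary outcomes will be analyzed using the chi-square test" and then lists Fisher's exact test, logistic regression, time-to-event analysis, the t test and the Mann-Whitney U test, the choice depending on the outcome. Site is not mentioned there.

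Table 2 lists 15 secondary endpoints. Ten are binary: nine at 30 days and mortality at 6 months. The other five are antibiotic days, quality of life, hospital stay, ICU stay and in-hospital costs. The Adverse events section adds that side effects and antibiotic resistance are followed as secondary endpoints, and it names no separate test for them.

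**The concern.** Blocking within centre balances the arms within each centre, so differences between centres largely cancel out of the treatment contrast. An unstratified test of a risk or mean difference still counts those differences as error. Its standard error is then larger than the true one, its size falls below nominal and its interval is wider than it need be.

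Centre differences are plausible here. The sites are university and non-university hospitals, cultures are processed in local laboratories, and *C. difficile* testing follows the attending physician's indication. Length of stay, antibiotic days and costs depend on local practice. A conservative test makes both a benefit and a harm somewhat easier to miss. The article recognises the stratification variable and then requires it for one endpoint only.

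**Working it through.** **Setting.** The only design figure in the article concerns the primary endpoint: "The sample size is calculated to be 966 patients". Inputs from the Sample size section: one-sided 2.5% error, 80% power, control risk 14%, and 40% reduction to 0.6 × 14% = 8.4%. With pooled variance under the null,

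n per arm = [1.96·√(2·0.112·0.888) + 0.8416·√(0.14·0.86 + 0.084·0.916)]² / 0.056² = 497,

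or 994 in total. The unpooled variant gives 988. Power with 483 per arm is 78.9%. The stated figure is thus reproduced to within 3% and serves below as the trial size. The article gives no power or sample size for any secondary or harm endpoint.

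**Assumptions not in the document.** ICC (the centre share of outcome variance), number of centres (6 or 12, equal size) and secondary event rates.

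**Size of the unstratified test.** If the true variance of the contrast is (1 − ICC) times the variance the test uses, the two-sided size is 2·[1 − Φ(1.96/√(1 − ICC))]. This gives 4.9% at ICC 1%, 4.8% at 2%, 4.4% at 5% and 3.9% at 10%. The test errs on the safe side.

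**Continuous endpoints.** Take 966 patients and a standardised difference of 0.18 (assumed, chosen to give about 80% power). The unstratified standard error is 2/√966 = 0.0643, so the expected z is 0.18/0.0643 = 2.797.

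- Unstratified power: Φ[(2.797 − 1.96)/√(1 − ICC)]
- Site-adjusted power: Φ[2.797/√(1 − ICC) − 1.96]

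| ICC | SE ratio √(1 − ICC) | Unstratified | Site-adjusted |
|---|---|---|---|
| 5% | 0.975 | 80.5% | 81.9% |
| 10% | 0.949 | 81.1% | 83.9% |

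The loss is about 1 to 3 points.

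**Binary endpoints.** Simulation of 20,000 trials per scenario: beta-distributed centre risks, 1:1 within centre, relative risk 0.6, Pearson chi-square against Cochran-Mantel-Haenszel (CMH). Power with 12 centres:

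| Control risk | ICC | Chi-square | CMH | SE ratio |
|---|---|---|---|---|
| 14% | 0 | 79.66% | 79.62% | 1.001 |
| 14% | 1% | 78.77% | 78.93% | 0.997 |
| 14% | 2% | 78.44% | 78.76% | 0.993 |
| 14% | 5% | 78.96% | 79.88% | 0.983 |
| 8% | 0 | 53.14% | 52.92% | 1.001 |
| 8% | 5% | 51.72% | 53.14% | 0.982 |
| 2% | 0 | 15.60% | 15.71% | 1.001 |
| 2% | 5% | 15.64% | 16.82% | 0.982 |

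Compare within rows; differences between rows include simulation noise. With 6 centres the gains at ICC 5% are 0.8, 1.0 and 1.0 points. Over ICC 1% to 5% the loss from ignoring centre is therefore about 0 to 1.5 points. Without centre variation there is none. The simulated size of chi-square at 14% risk and ICC 5% is about 4.4%, as the formula gives.

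The closed form √(1 − ICC) applied to binary outcomes is somewhat less favourable to the plan, with a loss of up to 2.0 points (8% risk, ICC 5%). It ignores that a relative risk of 0.6 shrinks the spread between centres in the treated arm, so the simulation is the better guide.

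**Log odds ratio scale.** In a separate simulation (10 centres, ICC 2%, 394 usable trials), adding centre to a logistic model raised the mean standard error from 0.2135 to 0.2159, about 1%, while the estimate moved from −0.581 to −0.594. The ratio of estimate to standard error goes from 0.581/0.2135 = 2.72 to 0.594/0.2159 = 2.75. Adjustment does not weaken the test, but it does not shrink this standard error either.

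**The case against.** The strongest reply is that the article gives a menu, not a fixed choice. Logistic regression and time-to-event analysis are on the list, both can carry site, and the text does not exclude it. Which covariates enter each secondary model is commonly settled in an analysis plan, and that plan is not shown. This stands to the extent that one cannot say the secondary endpoints will all be tested without site. It does not remove the point, because four named methods cannot use site as they are named. For costs and quality of life, the listed tests that fit most naturally are the t test and Mann-Whitney.

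A second reply also stands: the loss is small, most secondary endpoints are binary, no secondary power is promised, and the type I error stays at or below nominal.

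Three stronger readings are tempting and are not supported:

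- **That the interim test ignores site.** The Interim analysis section says only "The Z-statistic for the standardized treatment effect will be computed". A site-corrected model also yields a Z-statistic, and the primary analysis is described as site-corrected. The wording does not settle the matter either way.
- **That the planned standard errors are too large in general.** This holds for risk and mean differences, and only if centres differ. It does not hold for a log odds ratio.
- **That power is lost on a large scale.** This needs ICCs well above those used here, and the document gives no basis for them.

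**Conclusion.** The point holds as a minor one. The article requires the randomisation stratum in the primary analysis and leaves it out of the methods named for the secondary endpoints. The unstratified tests are valid. Where centres differ they are slightly conservative for risk and mean differences, at a cost of about 0 to 1.5 points of power for binary endpoints (ICC 1% to 5%) and about 1 to 3 points for continuous ones (ICC 5% to 10%).

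These figures rest on assumed ICCs, equal centres, an assumed relative risk of 0.6 and, for continuous outcomes, a standardised difference of 0.18. Mann-Whitney and Fisher's exact test were not simulated. The direction of the argument carries over to them; the figures do not.

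**What to change.** Add one sentence to the Statistical analysis section, or to the analysis plan if it does not already say so: secondary comparisons are stratified by or adjusted for study site where event counts allow. In detail:

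- Binary: Mantel-Haenszel risk difference or risk ratio with 95% confidence interval, and the Cochran-Mantel-Haenszel test.
- Continuous: a linear model with site, or a site-stratified rank test where the outcome is skewed, as stay and costs may be.
- Time-to-event: analysis stratified by site.
- Rare events: keep exact tests.

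The cost is wording only. Site is known for every patient from the stratified randomisation, so no new data and no extra patients are needed. If centres turn out not to differ, the simulations show no material loss (at most 0.3 points, 53.16% to 52.86% at 8% risk with 6 centres).
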